## 17. Pharmacovigilance

### 17.1 Definitions

**Adverse event (AE):** Any untoward medical occurrence in a subject to whom a medicinal product has been administered, including occurrences which are not necessarily caused by or related to that product. An AE, therefore, does not necessarily have a causal relationship with the treatment. In this context, “treatment” includes all investigational agents (including comparative agents) administered during the course of the trial. Medical conditions/diseases present before starting trial treatment are only considered adverse events if they worsen after starting trial treatment.

**Adverse Reaction (AR)/Adverse Drug Reaction (ADR):** Any untoward and unintended responses to an Investigational Medicinal Product (IMP) which related to any dose administered to that subject. All AEs judged by either the reporting investigator or the sponsor as having reasonable causal relationship to a medicinal product qualify as adverse reactions. The expression “reasonable causal relationship” means to convey in general that there is evidence or argument to suggest a causal relationship.

#### **Causality:**

The assignment of the causality should be made by the investigator responsible for the care of the participant using the definitions in the table below. All adverse events judged as having a reasonable suspected causal relationship to the IMP(s) (i.e. definitely, probably or possibly related) are considered to be adverse reactions. If any doubt about the causality exists, the Chief Investigator should be informed. In the case of discrepant views on causality between the investigator and others, all parties will discuss the case. In the event that no agreement is made, the MHRA, main REC and other bodies will be informed of both points of view.

| Relationship   | Description                                                                                                                                                                                                                                                                                                         |
|----------------|---------------------------------------------------------------------------------------------------------------------------------------------------------------------------------------------------------------------------------------------------------------------------------------------------------------------|
| Unrelated      | There is no evidence of any causal relationship                                                                                                                                                                                                                                                                     |
| Unlikely       | There is little evidence to suggest there is a causal relationship (e.g. the event did not occur within a reasonable time after administration of the trial medication). There is another reasonable explanation for the event (e.g. the participant’s clinical condition, other concomitant treatment).            |
| Possible       | There is some evidence to suggest a causal relationship (e.g. because the event occurs within a reasonable time after administration of the trial medication). However, the influence of other factors may have contributed to the event (e.g. the participant’s clinical condition, other concomitant treatments). |
| Probable       | There is evidence to suggest a causal relationship and the influence of other factors is unlikely.                                                                                                                                                                                                                  |
| Definitely     | There is clear evidence to suggest a causal relationship and other possible contributing factors can be ruled out.                                                                                                                                                                                                  |
| Not assessable | There is insufficient or incomplete evidence to make a clinical judgement of the causal relationship.                                                                                                                                                                                                               |

**Unexpected Adverse Reaction:** An adverse reaction the nature and severity of which is not consistent with the information about the medicinal product in question set out:- (a) In the case of a product with a marketing authorisation, in the Summary of Product Characteristics for that product; (b) in the case of any other investigational medicinal product, in the Investigator's Brochure relating to the trial in question.

**Serious Adverse Event (SAE) or Serious Adverse Reaction (SAR):** an adverse event, adverse reaction or unexpected adverse reaction, respectively, that (at any dose)-

- Results in death
- Is life-threatening (refers to an event in which the subject was at risk of death at the time of the event; it does not refer to an event which hypothetically might have caused death if it were more severe)
- Requires hospitalisation, or prolongation of existing hospitalisation
- Results in persistent or significant disability or incapacity
- Consists of a congenital anomaly or birth defect

Medical judgement should be exercised in deciding whether an AE/AR is serious in other situations. Important medical events that are not immediately life-threatening or do not result in death or hospitalisation but may jeopardise the patient or may require intervention to prevent one of the other outcomes listed in the definition above, should also be considered serious.

**Suspected, Unexpected Serious Adverse Reaction (SUSAR):** an adverse reaction that is both unexpected and serious. An adverse reaction is 'unexpected' if its nature or severity is not consistent with the applicable product information (see section 19.2).

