## **14.2 Number of Patients**

### **Cohort 1**

It is anticipated that there will be low numbers of treatment related adverse events in Cohort 1 and it is therefore both feasible and pragmatic to recruit 8 patients. It will be acceptable to move to cohort 2 as long as any unexpected treatment related adverse events are experienced in no more than 3 patients.

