### 17.4 Recording & Reporting Serious Adverse Events or Reactions:

All adverse events should be reported. Depending on the nature of the event, the reporting procedures below should be followed. Any questions concerning adverse event reporting should be directed to the Chief Investigator, Senior Trial Manager or Trial Manager in the first instance. A flowchart (figure 1) is given below to aid in the reporting procedures.

**Adverse Event (including Adverse Reaction):** All non-serious adverse events / reactions during drug treatment will be reported on the trial CRF. Severity of AEs will be graded on a three-point scale (mild, moderate, severe). Relation of the AE to the treatment should be assessed by the investigator at site. The Chief Investigator will be responsible for managing all adverse events/reactions.

**Serious Adverse Event / Reaction (SAE/SAR, including SUSARs):** All SAEs, SARs & SUSARs during drug treatment shall be reported to the Chief Investigator within 24 hours of the site learning of its occurrence. The initial report can be made by completing the serious adverse event CRF and faxing it via the SoHO66 fax to email system which will automatically send email notification to the Chief Investigator and to NCTU. In the case of incomplete information at the time of initial reporting, all appropriate information should be provided as follow-up as soon as this becomes available. Relationship of the SAE to the treatment should be assessed by the investigator at site, as should the expected or unexpected nature of any serious adverse reactions.

The MHRA and main REC will be notified by the Chief Investigator (on behalf of the Sponsor) of all SUSARs occurring during the trial according to the following timelines; fatal and life-threatening within 7 days of notification and non-life threatening within 15 days. SUSARs will be reported using a CIOMS 1 form, specifying the EudraCT number, CTA number, protocol number and trial name, and the data elements listed in Annex 3 of *Detailed guidance on the collection, verification and presentation of adverse reaction reports arising from clinical trials on medicinal products for human use – April 2006*.

All investigators will be informed of all SUSARs occurring throughout the trial on a case-by-case basis.

The Chief Investigator will ensure the Newcastle upon Tyne Hospitals NHS Foundation Trust as Sponsor is notified of any SUSARs in accordance with local trust policy.

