## **7. SAFETY ANALYSIS**

Most adverse events (AE) and adverse drug reactions that occur in this trial, whether they are serious or not, will be expected treatment-related toxicities due to the drugs used in this trial. For a full list of expected undesirable effects of CT327, please refer to the Investigator Brochure.

AE's are recorded by the clinical staff directly to the database on a three-point scale of severity (mild, moderate or severe) and also by causality (relationship to treatment categorised on a six point scale), as described in the protocol.

The analysis sets are the Phase 1b treatment set and the Phase 2a treatment set.

Any adverse events/reactions from start of treatment and up to the time of tumour excision (Phase 1b) or 4 weeks after end of treatment (Phase 2a), will be categorised according to severity and causality and recorded on the database.

The number of patients (Phase 1b) and tumours (Phase 2a) reporting any AE will be reported clarifying those deemed to be treatment related (Appendix 2).

In Phase 2a, the number of tumours with at least one AE will be reported as a proportion of the total number of tumours. The number of tumours with at least one treatment-related AE, that is those described as definitely, probably or possibly related, will be reported as a proportion of the total number of tumours. The number of tumours with at least one 'moderate' or 'severe' treatment-related AE will be reported as a proportion of the total number of tumours.

The unique number of patients experiencing at least one 'moderate' or 'severe' treatment-related AE will be reported as a proportion of the treatment set.

Proportions will be presented as % (95% CI).

Descriptions of the adverse events may require listing in the text.

No significance testing will be carried out.

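### Events graded 'Not assessable' for causality are by default handled as not related, both in SUSAR classification and in the SAP's treatment-related counts

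*Combined protocol and SAP*

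**What the plan says.** Protocol 17.1 grades causality as Unrelated, Unlikely, Possible, Probable, Definitely or Not assessable. The last is defined by lack of information: "There is insufficient or incomplete evidence to make a clinical judgement of the causal relationship". Three of the six grades make an event an adverse reaction: "i.e. definitely, probably or possibly related) are considered to be adverse reactions". A SUSAR is then defined as "an adverse reaction that is both unexpected and serious", so an event must first be an adverse reaction.

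SAP 7 records causality on the same six-point scale and counts as treatment-related only three grades: "that is those described as definitely, probably or possibly related". The adverse event table in SAP Appendix 2 splits treatment-related into 'Yes', with lines for those three grades, and 'No'.

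Protocol 14.2 and 14.3 allow the move to cohort 2 "as long as any unexpected treatment related adverse events are experienced in no more than 3 patients".

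Three provisions work the other way. Protocol 17.1 lets more than one party judge causality: "All AEs judged by either the reporting investigator or the sponsor as having reasonable causal relationship to a medicinal product qualify as adverse reactions". It also says: "If any doubt about the causality exists, the Chief Investigator should be informed". Protocol 17.4 makes the first serious-event report independent of causality: "All SAEs, SARs & SUSARs during drug treatment shall be reported to the Chief Investigator within 24 hours".

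**The concern.** A grade that means the evidence is insufficient is handled like a grade that means no relationship. That is the less cautious direction in the first study of CT327 in patients with CYLD defective skin tumours.

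Two things are at stake:

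- **Expedited reporting.** The 7-day and 15-day notifications in Protocol 17.4 apply to SUSARs. An event outside the adverse-reaction class does not enter that route by default.
- **Safety tables.** A reader of the SAP table cannot separate events judged unrelated from events nobody could judge.

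A third consequence, for cohort 1 progression, depends on which of several wordings governs.

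**Working it through.** The point concerns definitions, and the plan states no figure to reproduce. The check is to follow each grade through the documents.

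| Causality grade | Adverse reaction (Protocol 17.1) | Treatment-related (SAP 7) | Place in SAP Appendix 2 table |
|---|---|---|---|
| Definitely, Probable, Possible | Yes | Yes | 'Yes', one line each |
| Unlikely, Unrelated | No | No | 'No' |
| Not assessable | Not among the listed grades | Not among the listed grades | Only 'No' remains |

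**SUSAR route.** Protocol 17.4 asks for expectedness to be assessed for serious adverse reactions, and for MHRA and REC notification of SUSARs. A serious event graded 'Not assessable' reaches the Chief Investigator as an SAE within 24 hours. No sentence then requires an expectedness assessment or starts the 7- or 15-day period.

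**Do the safeguards supply a default?**

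- *Sponsor judgement.* 17.1 explains a reasonable causal relationship as one that some evidence or argument supports. An event graded for lack of evidence does not clearly meet that test.
- *Referral of doubt.* The Chief Investigator is informed, but no resulting classification or deadline is given. Both views go to the MHRA and REC only if the parties disagree; agreement that the event is not assessable triggers nothing.
- *Independence.* Protocol section 3 describes a single-centre trial and delegates the sponsor's pharmacovigilance, including SUSAR reporting, to the Chief Investigator, who is also responsible for conduct at the site.

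**Cohort 1 progression.** The criterion is worded in several ways:

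| Place | Basis | Uses causality grade? |
|---|---|---|
| Protocol 14.2, 14.3 | Unexpected treatment-related events in at most 3 patients | Yes |
| Protocol 6.1 | No unexpected trial-related site reactions, as indicated by modified Draize 3 or below, in at least 5 of 8 | The threshold is a score |
| Protocol, cohort 1 outcome measures | Number of severe skin reactions, plus DMC advice | No |
| SAP 8.4 | Number of severe skin reactions, with DMC guidance, citing the protocol's statistics section | No |

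SAP 8.1.1 and 8.2.1 count any Draize score of 4 or 5 whatever the causality grade. The effect is therefore confined to the first row, although SAP 8.4 points back to the protocol section containing that row.

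**Unit of change.**

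- Cohort 1: 1/8 = 12.5%.
- Cohort 2, patient level (15 to 20 patients): 1/20 = 5.0% to 1/15 = 6.7%.
- Cohort 2, tumour level: 1/150 = 0.7% overall, 1/75 = 1.3% per arm.
- Limit in 14.2 and 14.3: four affected patients, one graded 'Not assessable', count as 4 − 1 = 3 and meet the limit. Counted as four, they exceed it.

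**Illustration for the 14.2/14.3 wording only.** Let q be the chance that a patient has an unexpected event that would count if 'Not assessable' were included, and m the share of such patients lost to that grade. Neither is in the documents; both are assumed. With X ~ Binomial(8, q(1 − m)), the chance of meeting the limit is P(X ≤ 3):

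| q | m = 0 | m = 0.10 | m = 0.25 | m = 0.50 |
|---|---|---|---|---|
| 0.3 | 0.806 | 0.857 | 0.918 | 0.979 |
| 0.5 | 0.363 | 0.477 | 0.651 | 0.886 |
| 0.7 | 0.058 | 0.131 | 0.310 | 0.706 |

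The column m = 0 is what results if the grade is counted. The table shows sensitivity, not an expected effect.

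**The case against.** The strongest reply is that little is lost in practice. All serious events during treatment reach the Chief Investigator within 24 hours, incomplete reports must be followed up, the sponsor may also judge causality, and unresolved disagreement goes to the regulator and ethics committee. All six grades are recorded, and every event appears under 'Any AE'. The Appendix 2 table is a shell that does not define 'No'. Protocol 17.4 also cites a reporting flowchart that was not readable in the text reviewed. Much of this stands, and it rules out three stronger readings:

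- *That the expedited clock never starts.* A reader might infer this, but an investigator or the sponsor can upgrade the event at any time. The supportable statement is that the clock does not start by default.
- *That cohort 1 progression as such is compromised.* Only the 14.2/14.3 wording uses causality. In addition, SAP section 2 planned the DMC meeting on these data for 29 May 2015, while the protocol is version 3.0 of 16 May 2016. Unless those dates slipped by about a year, the decision has been taken.
- *That related-event rates are biased downward.* Leaving the grade out can only lower the count or leave it unchanged. Whether that departs from the truth depends on whether the events are really related, which the grade itself says is unknown.

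The reply does not supply a default. The safeguards leave the outcome to individual judgement, and the closed list of three grades decides when nobody acts.

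**Conclusion.** The gap is real and worth fixing. It comes from a stated closed list, not merely from missing detail. By default, 'Not assessable' events are grouped with unrelated ones in the safety tables, and serious unexpected ones fall outside the SUSAR class until someone upgrades them. This rests on the text of Protocol 17.1 and 17.4 and SAP 7, and on reading 'No' in the Appendix 2 table as everything not listed under 'Yes'. If the flowchart sets a default, the written definitions should say the same.

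The size of the effect cannot be stated, because the documents give no frequency for this grade. The fractions above show what one patient or tumour contributes; they are not effect estimates. The reporting and tabulation gaps apply to cohort 2. For cohort 1, what remains is mainly inconsistent wording of the progression criterion.

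**What to change.** - **Protocol 17.1:** state that 'Not assessable' events are handled as suspected adverse reactions for SAR and SUSAR classification, including assessment of expectedness, until reclassified.
- **SAP 7 and Appendix 2:** give 'Not assessable' its own row and report the treatment-related proportions both with and without it. Showing both avoids replacing one assumption with its opposite.
- **Protocol 14.2 and 14.3:** reconcile these with Protocol 6.1, the cohort 1 outcome measures and SAP 8.4, and say how the grade counts wherever causality is used.
- **Protocol 17.3 and 17.4:** align them. 17.3 speaks of recording non-serious reactions and 17.4 of reporting non-serious events and reactions; read alone, 17.3 would leave out a non-serious 'Not assessable' event.

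The core change costs one sentence in the protocol, one in the SAP and one table row; the two alignments are further small edits. The downside is an occasional extra expedited report and slightly less favourable related-event rates in the version that includes the grade.

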### **Severity (intensity) of Adverse Events and Adverse Reactions**

Severity of all AEs and ARs will be graded on a three-point scale of intensity (mild, moderate, severe):

- Mild: Discomfort is noticed, but there is no disruption of normal daily activities.
- Moderate: Discomfort is sufficient to reduce or affect normal daily activities.
- Severe: Discomfort is incapacitating, with inability to work or to perform normal daily activities.

An AE or AR may be severe but not serious

## **17.2 Expected adverse reactions:**

Most adverse events and adverse drug reactions that occur in this trial, whether they are serious or not, will be expected treatment-related toxicities due to the drugs used in this trial. For a full list of expected undesirable effects of CT327, please refer to the Investigator Brochure.

The dose of CT327 to be used in this trial 0.5% as well as a dose of 0.05% have been used previously and were well tolerated by patients. In total 322 patients and 36 healthy volunteers have previously been treated with CT327 ointment and creams. The negative events that have been reported in previous studies include:

|          |    |
|----------|----|
| Pruritus | 6% |
| Eczema   | 6% |

|                                   |    |
|-----------------------------------|----|
| Headache                          | 5% |
| Nasopharyngitis                   | 3% |
| Diarrhoea                         | 3% |
| Application site pruritus         | 3% |
| Application site reactions        | 3% |
| Rhinitis                          | 2% |
| Upper respiratory tract infection | 2% |
| Cough                             | 2% |
| Back Pain                         | 2% |
| Dermatitis atopic                 | 2% |
| Dermatitis                        | 1% |
| Rash                              | 1% |
| Psoriasis                         | 1% |
| Fatigue                           | 1% |
| Vomiting                          | 1% |

CT327 has not been detected in the blood of any subjects treated with CT327 cream or ointment.

### 17.3 Protocol Specifications

For purposes of this protocol:

- All non-serious adverse reactions will be recorded at all trial visits
- Any serious adverse events will be recorded throughout the duration of the trial until the final trial visit.
- Serious adverse events exclude any pre-planned hospitalisations (e.g. elective surgery) not associated with clinical deterioration.
- Serious adverse events exclude routine treatment or monitoring of the studied indication, not associated with any deterioration in condition.
- Serious adverse events exclude elective or scheduled treatment for pre-existing conditions that did not worsen during the trial.
- Serious adverse events exclude increases in tumour size [primary outcome measure, already documented and monitored within trial]

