| Primary objective:     | To determine the safety of CT327 application in CYLD mutation carriers                                                                                                                                                                                                                                                                                           |
| Primary Outcome:       | Number of patients with severe treated skin site reactions as determined by Modified Draize score                                                                                                                                                                                                                                                                |
| Secondary Outcome:     | 

a. Patient reported quality of life using patient reported QoL tools (EQ5D, DLQI)

b. Acceptability of treatment according to patient treatment questionnaire (Appendix B).

c. Adverse events within a planned 4 week treatment period

d. Compliance including reasons for non-compliance

 |
| Number of trial sites: | 1                                                                                                                                                                                                                                                                                                                                                                |
| Trial population/size: | 8                                                                                                                                                                                                                                                                                                                                                                |

## 4.2 Cohort 2

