| Primary outcome:       | The proportion of tumours responding to treatment by 12 weeks.                                                                                                                                                                                                                                                                                                                                                                                                                                                                                                                                                                                                                                                                                                                                                                                                                                   |
| Secondary outcomes:    | 

a. Change in tumour volume from baseline (pre-randomisation) to 12 weeks

b. Adverse events within a planned 12-week treatment period

c. Compliance including reasons for non-compliance

d. Confirmation of the definition of response (currently according to WHO RECIST criteria where response is defined as >30% reduction in tumour volume, this will be used as a benchmark).

e. Expression of targets of TRK signalling in tumour biopsies as determined by QPCR and immunohistochemistry.

f. Patient reported quality of life using patient reported QoL tools (EQ5D, DLQI)

g. Assessment of acceptability of trial treatment according to patient treatment questionnaire (Appendix B).

h. Patient reported pain using the Patient Pain Assessment Form at 0, 4 and 12 weeks.

 |

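### Protocol 17.3 sets the recording of non-serious events at adverse reactions, while 17.4, the schedules, the secondary outcomes and SAP 7 need all adverse events, and nothing says which rule prevails

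*Combined protocol and SAP*

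**What the plan says.** Protocol 17.3 lists rules that apply for the purposes of the protocol. The first covers non-serious events: "All non-serious adverse reactions will be recorded at all trial visits". The second covers serious ones: "Any serious adverse events will be recorded throughout the duration of the trial until the final trial visit". So the non-serious rule is written for reactions and the serious rule for events.

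Protocol 17.1, under Causality, gives the boundary between the two terms. Events with a reasonable suspected causal link ("i.e. definitely, probably or possibly related) are considered to be adverse reactions") count as reactions. The causality table has six categories. The other three are unrelated, unlikely and not assessable.

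Protocol 17.4 is wider. It opens with "All adverse events should be reported" and then states: "All non-serious adverse events / reactions during drug treatment will be reported on the trial CRF". The visit lists in 13.4 and the schedules in 13.7 and 13.8 also carry an adverse events entry, with no restriction to reactions.

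Adverse events are a secondary outcome in both cohorts: "Adverse events within a planned 4 week treatment period" for cohort 1 (section 4.1) and "Adverse events within a planned 12-week treatment period" for cohort 2 (section 4.2).

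SAP section 7 grades causality on a six-point scale and counts Phase 2a events up to 4 weeks after treatment ends. For Phase 2a it plans that "the number of tumours with at least one AE will be reported as a proportion of the total number of tumours", and it reports treatment-related events as a separate proportion. The adverse event table in SAP Appendix 2 has an any-AE row and a treatment-related split into yes and no.

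**The concern.** If 17.3 is read as the recording rule, the investigator's opinion on causality decides whether a non-serious event enters the database at all. The SAP treats causality differently, as a field recorded about an event that is already there.

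Three things would be at stake.

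- Any AE is the safety summary that depends least on causality judgement. In cohort 2, for local events, it can be set side by side for the active and placebo sides of the same patient. Restricted to reactions, it adds almost nothing to the treatment-related count.
- Section 17.1 lets either the investigator or the sponsor judge an event related, and provides for differing views to be discussed. Neither safeguard can work on an event that was never written down. This is the first use of CT327 in this disease (section 10.1), so a second look at causality has some value.
- If staff apply the two sections differently, the database will not show which rule lay behind a given record.

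**Working it through.** The documents give no figure to reproduce, and the point does not depend on sample size or error rates. The check sets the passages side by side.

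**Scope of non-serious events**

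| Source | What is to be recorded or reported |
|---|---|
| Protocol 17.3, first bullet | Reactions |
| Protocol 17.4 | All events and reactions |
| Protocol 13.4, 13.7, 13.8 | Adverse events |
| Protocol 4.1 and 4.2, secondary outcomes | Adverse events |
| SAP 7 and Appendix 2 | Any AE, with treatment-related as a subset |

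Step 1. By 17.1, reactions are the definite, probable and possible categories: 3 of 6. The categories outside the term are 6 − 3 = 3: unrelated, unlikely and not assessable.

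Step 2. SAP 7 defines a treatment-related AE by the same three categories. For non-serious events, the 17.3 set and the SAP treatment-related set are therefore identical.

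Step 3. If 17.3 alone governed collection, then for non-serious events any AE = treatment-related AE. The *No* row of the treatment-related split in Appendix 2 could hold serious events only.

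Step 4. If 17.4 governs, all six categories are recorded during treatment and the SAP table can be filled as designed.

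**Time window, Phase 2a**

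Step 5. Treatment lasts 12 weeks, and SAP 7 counts events to 4 weeks after it ends, so the SAP window is 12 + 4 = 16 weeks. The specific 17.4 sentence on non-serious events is limited to drug treatment, which leaves 4/16 = 25% of the window outside it.

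Step 6. For those 4 weeks, full capture rests on the general opening line of 17.4 and on the adverse events entry for the follow-up call in 13.8. The 17.3 bullet speaks of visits, and this contact is a telephone call. The text on the call in 13.4 aims it at significant adverse events, and at site reactions and side effects.

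Step 7. In cohort 1 the SAP window ends at tumour excision. Protocol 13.4 places surgery at the week 4 visit, so there is little or no such gap.

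**The case against.** The strongest reply is that 17.3 uses one loose word and that the rest of the documents are clear. It does not say *only*, and it forbids nothing. A site that records every adverse event complies with 17.3 and 17.4 together. The schedules ask for adverse events, and the six-point scale in the SAP shows that unrelated events are expected in the database. All of this stands, and it makes the consequence conditional: the documents do not show that data will be missing.

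It does not remove the conflict. The contrast within 17.3 between non-serious reactions and serious events can be read as a deliberate scope rule. The title of 17.4 refers to serious events, so a reader looking for the non-serious rule may stop at 17.3. No ranking of the two sections is given.

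A reader might also infer two stronger things that the documents do not support.

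- *That unrecognised signals would never reach the database or the DMC.* Serious events are recorded whatever their cause, even under 17.3. A possible relation is enough to make an event a reaction. Section 15.2 has other reported side effects assessed by the chief investigator.
- *That the loss can be sized from the list of earlier events in 17.2.* The listed percentages add to 44, of which the non-skin items make 5+3+3+2+2+2+2+1+1 = 21. The ratio of the two is not a share of events lost. The percentages are per term and can overlap within a subject. The list stands under a heading of expected reactions. Whether an event affects the skin is no guide to how its causality would be judged. Systemic events also cannot be compared between sides, because every cohort 2 patient uses both ointments.

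**Conclusion.** The inconsistency is real and lies in current, operative text. Protocol 17.3 is narrower than 17.4, the schedules, the secondary outcomes and SAP 7, and nothing says which prevails.

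The effect depends on which section staff follow. Under 17.4 nothing is lost during treatment. Under 17.3, taken as the scope rule, non-serious events in three of six causality categories are not recorded, and the planned distinction between any AE and treatment-related AE disappears for non-serious events. In addition, the specific 17.4 sentence leaves out the last 4 of the 16 weeks that SAP 7 counts in Phase 2a.

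The number of events involved cannot be derived from the documents. The modified Draize and tumour response outcomes are not affected. The cohort 1 progression count in 14.3 uses unexpected treatment-related events, which 17.3 keeps; only the chance to re-examine events first judged not related would be lost. The reporting flowchart that 17.4 mentions could not be seen and may add detail.

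**What to change.** Reword the first bullet of 17.3 along these lines: *All non-serious adverse events, whether or not judged related, will be recorded at all trial visits and contacts, up to tumour excision (cohort 1) or 4 weeks after end of treatment (cohort 2).*

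Extend the window in the 17.4 sentence on non-serious events to agree with SAP 7. Keep causality as a separate field on the CRF, so that the SAP can derive both counts from one record. The cohort 2 outcome is worded for the 12-week treatment period, so SAP 7 should also state whether events in the 4 follow-up weeks are tabulated with that outcome or separately.

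The cost is a short protocol amendment, a clarifying line in the SAP, and slightly more CRF entry for 8 patients in cohort 1 and 15–20 in cohort 2. The change concerns data capture only.
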